# Evaluation of a self-help intervention to promote the health and wellbeing of marginalised people including those living with leprosy in Nepal: a prospective, observational, cluster-based, cohort study with controls

**DOI:** 10.1186/s12889-021-10847-0

**Published:** 2021-05-06

**Keywords:** Leprosy, Ulcers, Disability, Low and middle-income countries, Self-care, Self-help groups, Self-management, Economic improvement

## Abstract

**Background:**

People affected by leprosy are at increased risk of ulcers from peripheral nerve damage. This in turn can lead to visible impairments, stigmatisation and economic marginalisation. Health care providers suggest that patients should be empowered to self-manage their condition to improve outcomes and reduce reliance on services. Self-care involves carrying out personal care tasks with the aim of preventing disabilities or preventing further deterioration. Self-help, on the other hand, addresses the wider psychological, social and economic implications of leprosy and incorporates, for example, skills training and microfinance schemes. The aim of this study, known as SHERPA (Self-Help Evaluation for lepRosy and other conditions in NePAl) is to evaluate a service intervention called Integrated Mobilization of People for Active Community Transformation (IMPACT) designed to encourage both self-care and self-help in marginalised people including those affected by leprosy.

**Methods:**

A mixed-method evaluation study in Province 5, Nepal comprising two parts. First, a prospective, cluster-based, non-randomised controlled study to evaluate the effectiveness of self-help groups on ulcer metrics (people affected by leprosy only) and on four generic outcome measures (all participants) - generic health status, wellbeing, social integration and household economic performance. Second, a qualitative study to examine the implementation and fidelity of the intervention.

**Impact:**

This research will provide information on the effectiveness of combined self-help and self-care groups, on quality of life, social integration and economic wellbeing for people living with leprosy, disability or who are socially and economically marginalised in low- and middle- income countries.

**Supplementary Information:**

The online version contains supplementary material available at 10.1186/s12889-021-10847-0.

## Background

### Self-care and self-help

Nerve damage in leprosy leads to a loss of sensation in limbs and around the eyes and inhibits normal sweating which results in the skin becoming dry and fragile. These factors increase the risk of accidental injury and the development of wounds (ulcers) which tend to become infected. Nerve damage can lead to physical disability, either directly or as a result of deep seated infection [1, 2].

In order to promote healing of ulcers and prevent recurrence, people with nerve damage are encouraged to practice self-care. Self-care involves supporting people and teaching them how to look after their hands and feet to prevent and manage ulcers. This incorporates a process of inspecting, soaking, scraping and oiling skin, and dressing wounds. The aim is to keep skin and wounds clean, callus free and well moisturised. Self-care has been found to be successful in preventing the occurrence and recurrence of ulcers [3, 4].

While self-care alleviates the pathophysiological complications of leprosy, the emphasis in self-help is on the socio-economic consequences of the disease. Leprosy is a disease associated with poverty and ultra-poverty (living on less than $0.5 per day) and those who are affected may be even further economically disadvantaged by disability and stigma [5]. Thus, the aim of self-help groups is to assist people to improve their social and economic circumstances by promoting economic self-reliance, social participation and through advocacy [6]. Self-help interventions often include promotion of savings syndicates, provision of seed-corn money, improving skills and know how, and introductions to wider commercial networks.

Self-management interventions may incorporate self-help as in the intervention described in this paper. Organisations concerned with the management of leprosy have widened their remit, and support self-management schemes that include people with disabilities other than leprosy and also people who are simply marginalised with no medical condition.

Two self-management interventions have been previously conducted in Nepal. The CEDAR (Community Empowerment, Development, Disability and Rehabilitation) project [7] ran between 2009 and 2014 in Rautahat (Province 2) and Ramechhap (Province 3), and the PACED (Participatory Action for Community Empowerment and Development) project (unpublished) from 2014 to 2019 in Parsa (Province 2), Chitwan (Province 3) and Makwanpur (Province 3). Although these interventions were viewed as successful, and retrospective (mainly qualitative) evaluations were conducted [7], the results have not been published in the academic literature.

A recent scoping review [8] of community-based self-management interventions among groups that included people affected by leprosy noted 10 studies that reported successful health-related outcomes but none of these were controlled studies. Notwithstanding a recent initiative to promote research in leprosy [9], the evidence base on leprosy-related community interventions is limited and situated primarily in the grey literature. This prospective study thus provides a unique opportunity to develop the evidence on self-care and self-help on clinical, social and economic outcomes in marginalised people.

### Integrated mobilization of people for active community transformation (IMPACT)

The IMPACT programme in Nepal is a five-year self-help and self-care project scheduled to roll out across three districts (Nawalparasi West, Rupandehi and Kapilbastu) in Province 5. Initially designed for people affected by leprosy, the programme has expanded to include other marginalised people, including those with other types of disability (e.g. Lymphatic Filariasis: LF) and people with no disease or disability but who live in extreme poverty. The programme strives to recruit an equal balance of males and females. Participants include people affected by leprosy, people affected by disability or who care for a person with disability and people who are marginalised in other ways. Marginalised people include single women and those with a daily income below $1.9. IMPACT also targets the wider community using advocacy to change negative perceptions of marginalised people and stigmatisation of people with physical or mental illness.

The aim of the intervention is for individuals to gain knowledge and skills to improve their quality of life. This will be achieved through the formation of 36 self-help groups, which, it is hoped, will become self-sustaining ‘co-operatives’ over time. In summary, individuals will be encouraged to participate in group activities including self-care and income generating activities, to improve their health, wellbeing, social integration and economic status. A self-help causal pathway for the IMPACT intervention is proposed in Fig. 1.

**Fig. 1 Fig1:**
[figure not shown]
Proposed self-help causal pathway

### IMPACT implementation

The IMPACT intervention is implemented by facilitators employed by The Leprosy Mission (TLM) Nepal. They form a link between the overall governance and management of the programme, and the individual self-help groups in their rural communities. It is the function of the facilitators to bring self-help groups into existence and then mentor their performance. The groups relate to a health outpost in an area of known high prevalence (based on registers of people affected by leprosy and other chronic conditions held at each outpost). About 25 people will be invited to participate in each group and we expect 20 people to ‘sign up’ for the group in each cluster. Facilitators attend group meetings, which will be held fortnightly for three months, and then monthly. The groups elect leaders (chairperson, vice-chairperson, secretary and treasurer), half of whom must be women. These leaders can be changed after two years if necessary. Leaders are given specific training over a three-day period which includes basic accounting, and each group is given assistance to open a bank account. As groups mature, a second ‘layer’ of facilitators are elected to form a ‘bridge’ between the TLM facilitators and the individual groups (Fig. 2).

**Fig. 2 Fig2:**
[figure not shown]
Disbursement of human resources responsible for implementing, mentoring and consolidating the self-care and self-help intervention

### IMPACT intervention components

The intervention components are described in Table 1.

**Table 1 Tab1:** Key components of the IMPACT intervention

Key components	Comments
Group membership	Up to 25 participants, equal numbers of sexes, approximately half of participants affected by leprosy.
Meeting frequency	Sessions lasting approximately 2 h will be held fortnightly for three months and then monthly thereafter.
Facilitation	Three trained facilitators will establish 36 self-help groups. Facilitators will move between groups to provide training in their own speciality area, e.g. budgeting, bookkeeping, wound care. Key tasks include recruitment, encouraging attendance, maintaining registers of group members and activities, monitoring loan repayment, problem solving, engaging in advocacy with influential people in the community.
Peer leadership	The groups will elect four leaders (chairperson, vice-chairperson, secretary and treasurer), half of whom must be women. Leaders can be changed after 2 y if necessary. Leaders will be trained in basic accounting and each group will be given assistance to open a bank account.
Mutual support	Members will be encouraged to share their experiences, support each other and learn from each other.
Encouraging self-care* practices	Facilitators will ensure that group members have appropriate tools and equipment; observe self-care activities and encourage diligence; and encourage early referral to health facilities where necessary.
Tool provision*	Simple tools and equipment will be provided (e.g. mirrors to inspect the plantar surface of the foot, basins for soaking limbs in tap water, crutches, etc.)
Shaping knowledge	Group discussions to include: provision of disability cards, gender violence, civil rights, disaster preparedness. Members will be provided with information and encouraged to adopt healthy behaviours including Water, Sanitation and Hygiene (WASH).
Economic empowerment	Saving credit schemes will be facilitated. Seed money will be provided to establish enterprises. Business awards may be granted after skills training. Groups will be facilitated to become co-operatives that qualify to join the broader co-operative infra-structure in Nepal. Membership of this national, official, collaborative structure confers certain opportunities, such as advice, support and networking opportunities.
Livelihood and skill training	Training will be provided including organic farming, animal husbandry, basic accountancy, sewing, hairdressing.
Advocacy	The facilitators make contact with elected village chiefs, traditional healers, religious leaders and female community health volunteers to advocate for group members.
Ownership	Groups will be autonomous and able to direct and modify their training needs and activities. They will be encouraged to innovate. Past examples include use of games that have been designed for differently abled people and ‘street drama’.

* Only for people affected by leprosy

These components are not administered simultaneously, but are rolled out over time, as shown in Fig. 3.

**Fig. 3 Fig3:**
[figure not shown]
Phasing of the Intervention

The IMPACT intervention was developed by The Leprosy Missions Nepal and Australia, using behavioural science principles. The evaluation team had no part in its development.

The IMPACT intervention is funded by the Australian government at US $150,000 per year for 5 y. This paper describes the independent ‘rapid response’ [10].

## Methods

The SHERPA (Self-Help Evaluation for lepRosy and other conditions in NePAl) study forms part of a wider programme of work under an NIHR Research and Innovation for Global Health Transformation (RIGHT) grant which covers long-term care and prevention of leprosy ulcers in three low-income countries (India, Nepal and Nigeria) and a study of participants with a disease called Buruli ulcer (in Nigeria only). This protocol reports on the evaluation of the IMPACT service intervention in Nepal only.

### Study setting

We will study 18 villages (clusters) of the 36 in the IMPACT self-help intervention in Province 5, Nepal. These villages are selected because they had not already started to implement the IMPACT intervention at the point where ethical clearance for this protocol was obtained. This timing provides an opportunity to conduct a prospective evaluation with baseline, midline and end line observations.

### Study design

The study is a prospective, evaluation of self-help in the selected clusters. We will conduct mixed methods, non-randomised controlled study with observations at baseline, end line and at points in between. People who join the self-help group will form the intervention group (*n* ~ 18*20 = 360). A control group will be obtained from the same clusters as the self-help group (*n* ~ 360). Both groups, intervention and control will be followed up as a cohort. The study will include quantitative observations at baseline and follow up along with qualitative observations with an emphasis on context, the process of implementation and causal mechanisms. Quantitative observations made from all participants (*n* ~ 720) across both groups are of four types: health, wellbeing, social integration and economic wellbeing. These will be made in the self-help groups and control groups. Clinical observations will also be made among the cohort of people affected by leprosy in the self-help group. Since people affected by leprosy are not eligible for the control group, these observations will be made only in the self-help group. Some people affected by leprosy and eligible for the self-help intervention may decline to participate in the self-help group. Any such people will be offered entry into a small, second control group of unknown size described below. The qualitative observations will include observations of both intervention group members, members of the wider community and of senior stakeholders.

### Eligibility criteria

The intervention group (self-help group) will consist of adults at with or at risk of a leprosy ulcer, another chronic disabling condition or who are marginalised by extreme poverty (as defined above). Eligible people will be invited to take part in an IMPACT self-help group. This process is conducted by the IMPACT intervention team independently from the research team who have no part in the process.

In Nepal, administrative districts are subdivided into municipalities, then wards, then villages. The IMPACT intervention clusters are created at the level of wards in six municipalities across the three districts (Nawalparasi West, Rupandehi and Kapilbastu) of Province 5. Fig. 4 shows the location of the numbered wards within their respective municipalities and districts. The pink shaded circles in each ward represent the self-help group clusters. Within those clusters, the numbered locations represent adjoining villages, from which prospective self-help group members are recruited.

**Fig. 4 Fig4:**
[figure not shown]
Location of clusters

Figure 4 shows where Provence five is located within Nepal, then the three clusters that comprise the Provence and then the 18 clusters that are taking part in the SHERPA study. Note clusters may include a number of villages from which members of self-help groups (and controls) are selected.

For comparison purposes, we will generate two additional groups resident in the same clusters as the intervention (self-help group) members. Generating those groups involve collaboration between the IMPACT intervention team and the research group. See Fig. 5.

**Fig. 5 Fig5:**
[figure not shown]
Self-help intervention group decision tree

Control group 1 will be comprised of individual adults (over 18 years of age) who are not eligible to take part in the self-help groups in a particular cluster.

We do not have access to the details of all residents in a cluster, so we cannot directly select people at random to form a counterfactual group to the intervention group. However, we do have access to the details of the households in each cluster. We will therefore start by selecting households at random. The intervention facilitator will obtain a list of all households in the cluster and remove those who are eligible for the self-help intervention from the list. An anonymised list of households will be provided to the study co-ordinator who will randomly select 35 households and place them in a numbered list.

In line with the intervention group, the researcher will identify an adult member of each selected household who is able to answer questions relating to the household’s consumption. The researcher will meet with the identified adults, singly or in groups, to explain the purpose of the study. Each potential participant will be approached individually to seek consent. If the individual declines, then no further action will be taken and the researcher will move on to the next household. The researcher will stop recruiting when approximately 20 people have been recruited from 20 households.

Control group 2 will comprise people who were eligible for the intervention, who declined to participate in the self-help groups, but who nevertheless agree to provide data for the evaluation. It is thus possible, or even likely, that there will be no second control group in some clusters.

### Ethics and consent

Eligible people will be provided with a Participant Information Sheet in local languages. Information will be provided verbally for participants who are non-literate. Written informed consent will be obtained from all participants; or thumb/fingerprints will be requested in lieu of a signature if necessary. Translated consent forms will be back-translated according to the WHO recommendations [11] for quality assurance purposes. Participants will be free to withdraw at any time. Ethics approval for the study has been granted locally in Nepal through the Nepal Health and Research Council (NHRC-approval number 444–2020 P) and by the University of Birmingham Biomedical and Scientific Research Ethics Committee (BSREC).

### Aim of the evaluation

The aim of the SHERPA evaluation is to determine whether the IMPACT intervention achieves its aims to improve health and wellbeing, social functioning and economic status. We hypothesise that:
Participants who receive the IMPACT intervention will experience greater improvement over time in the four universal outcome measures (generic health, subjective wellbeing, social participation and economic status) than people in control group 1.People affected by leprosy will experience a lower prevalence and severity of ulcers after the intervention than before.

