### Quantitative data

*Health, social and economic wellbeing (all participants)*

The four generic outcome measures are:
i.Generic health status (quality of life). Data will be collected using a standardised instrument, the EQ-5D-3L [12]. A country specific digital version will be used. As far as we are aware, there is no valuation tariff in the Nepalese population, although this may change by the time that the analysis starts. Therefore, we propose not to pre-specify the tariff but instead select the tariff at a later date. We note that tariffs are currently available for nearby countries including Sri Lanka [13] and China [14, 15].ii.Subjective wellbeing data. Data will be collected using a standardised five question instrument [16, 17] designed to capture evaluations of the participant’s level of life satisfaction, an evaluation of personal meaning and happiness, and their affective state.iii.Social integration. Data will be collected using the validated participation scale (p-scale) [18] which has been used in rehabilitation, stigma reduction and social integration programmes in low- and middle-income countries (LMICs). A Nepali language version is available.iv.Economic status will be measured by examining total household consumption. A consumption questionnaire has been derived from Sections 2, 5, 6 and 7 of the Nepal: Living Standards Survey (NLSS: 2011/12) [19]; see Additional File 1. The NLSS is a multi-topic household survey conducted by the Central Bureau of Statistics (CBS) of the Government of Nepal in conjunction with the World Bank which in turn is part of the Living Standards Measurement Surveys (LSMS) conducted by the World Bank. We have chosen to measure consumption rather than wealth or income for the following reasons. 1) Measuring income in LMICs is affected by fluctuations due to the informal nature of work and seasonal activity [20], while consumption is more stable over time [20, 21]. Asset (wealth) indices may be more stable [22] but are likely insensitive to change over the short-term observation period of this study.2.*Clinical Data (people affected by leprosy in intervention group and control group 2)*

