## Discussion

The purpose of the study is to evaluate the effectiveness of the IMPACT self-help group on the health, wealth and wellbeing of marginalised people, including those affected by leprosy. However, there are challenges in the design and approach considered.

The evaluation design has been applied to an existing programme whose roll out has already begun. Moreover, follow up is limited at 24 months because of the duration of the funding envelope. We therefore will not be able to measure how effects may manifest in the longer term. If no effect is observed within the scope of this study, then arguably it is unlikely that one would arise later, especially as we complete our study only shortly before the end of the funded intervention phase. However, we will seek further funds to study sustainability if the findings point towards effectiveness.

It is possible that the observations we make could have an effect, perhaps augmenting the ‘dose’ of any intervention effect. This putative Hawthorne type effect could be observed by making only end-line observations in some clusters. We do not have resources to do so. Furthermore observations will be made in both intervention and control groups, so any reactivity would be equal across groups absent and interaction between the extent of any reactivity and the intervention.

While we have internal controls for health, wellbeing, social and economic data, we obtain clinical data only from people affected by leprosy and people are excluded from control group 1 by design. However, where people affected by leprosy choose not to participate in the intervention, perhaps due to stigma, but nevertheless elect to participate as a member of control group 2, we will be able to collect clinical data. Insofar as these numbers will be small, we may not be able to obtain precise contemporaneously controlled data and will have to rely on before and after comparison. However, we are looking for a much bigger effect on ulcers than on economic change. Moreover, the risk of a temporal trend is greater for the economic and social indicators than for the clinical indicators. Nepal is a developing country so a temporal trend in economic development is to be expected. Absent contemporaneous controls this could lead to a spurious or over-estimated benefit. It was for this reason that we have implemented control groups.

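### The ulcer hypothesis is an uncontrolled before-after comparison that the Abstract presents as controlled, and the sections disagree on whether control group 2 is examined clinically

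*Protocol article*

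**What the plan says.** All references are to the protocol article.

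- **Abstract, Methods:** the quantitative part is a "non-randomised controlled study to evaluate the effectiveness of self-help groups on ulcer metrics" and on four generic outcomes.
- **Aim of the evaluation:** the generic outcomes are compared with control group 1. The ulcer hypothesis has no comparator: "People affected by leprosy will experience a lower prevalence and severity of ulcers after the intervention than before".
- **Eligibility criteria:** the people affected by leprosy who can join are "adults at with or at risk of a leprosy ulcer", so a current ulcer is one way in and being at risk is another.
- **Study design:** people affected by leprosy cannot enter the control group, so "these observations will be made only in the self-help group". The next sentences introduce a second control group for those who decline.
- **Quantitative data:** the clinical heading reads "Clinical Data (people affected by leprosy in intervention group and control group 2".
- **Discussion:** clinical data can be collected in control group 2, but numbers will be small, so the analysis may have to rest on before against after. Two reasons are offered: the effect sought on ulcers is much bigger than on economic outcomes, and "the risk of a temporal trend is greater for the economic and social indicators than for the clinical indicators".

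**The concern.** There are two linked problems.

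First, the label does not match the test. A reader of the Abstract expects the ulcer result to be protected by a control group, as the generic outcomes are. It is not.

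The Discussion's defence deals with secular trend. For a condition that heals and recurs, as the Background describes, the nearer threat is different. If people who have an ulcer at the time join more readily than people who are only at risk, prevalence at T0 sits above its long-run level and drifts down without any intervention. A larger expected effect does not separate that drift from benefit, and the article's precision statement (Power calculation and sample size) lists expenditure, wellbeing and health status, not ulcers.

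Second, a field team that followed Study design literally would not examine people affected by leprosy in control group 2. That group is the only concurrent source of ulcer data, and a missed T0 examination cannot be recovered.

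**Working it through.** **The plan's own numbers.** 18 clusters × 20 = 360 members, and 2 × 360 = 720 with control group 1. Both match Study design. Table 1 has about half of members affected by leprosy, so about 360 / 2 = 180 contribute to the ulcer hypothesis. The article states no ulcer prevalence, effect size or precision, so no ulcer figure can be reproduced.

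**Illustration of the before-after problem (assumed inputs).** Take a two-state model with no intervention effect. Let π be the long-run ulcer prevalence (assumed 20% or 30%), s the share with an ulcer at T0, and r the correlation of a person's ulcer status between T0 and T2 (assumed 0.3 or 0.6).

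Expected T2 prevalence = π + r(s − π), so the expected fall = (1 − r)(s − π).

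The chance of a nominally significant fall uses the normal approximation to McNemar's test, n = 180, two-sided 5%, ignoring clustering. It is a yardstick only, since the planned analysis is Bayesian.

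| Excess at T0, s − π | Expected fall, no effect | Chance of a significant fall |
|---|---|---|
| 0 points | 0 points | 2.5% |
| 10 points | 4 to 7 points | 24 to 44% |
| 20 points | 8 to 14 points | 67 to 93% |
| 30 points | 12 to 21 points | 94 to 99.9% |

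**Where the fall comes from.** With π = 0.20 and r = 0.3, the chance of being ulcer-free at T2 after an ulcer at T0 is 1 − (0.20 + 0.3 × 0.80) = 0.56. The chance of an ulcer at T2 after none at T0 is 0.20 × 0.7 = 0.14.

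- If s = 0.20: healed 0.20 × 0.56 = 0.112; new 0.80 × 0.14 = 0.112. Net change is zero.
- If s = 0.40: healed 0.40 × 0.56 = 0.224; new 0.60 × 0.14 = 0.084. Net fall is 0.14.

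The healing and new-ulcer rates are identical in the two cases. Only the mix at entry differs, so that mix has to be reported.

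**What control group 2 could add.** From IMPACT implementation, about 25 people are invited and 20 join, so decliners number at most about 18 × (25 − 20) = 90. If half are affected by leprosy, that is 45, and it requires every decliner to consent. With 30% prevalence in both groups, the 95% half-width of the T2 difference is 1.96 × √(0.21/180 + 0.21/m), ignoring clustering:

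- m = 5: 41 points
- m = 10: 29 points
- m = 20: 21 points
- m = 36: 16 points
- m = 45: 15 points

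**The contradiction.** Study design confines clinical observations to the self-help group. Quantitative data and the Discussion add control group 2. These cannot both be carried out as written.

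**The case against.** The strongest reply is that nothing is hidden. The hypothesis says before and after in plain terms, and the Discussion openly accepts the reliance on it. That stands. A reader might infer concealment, but the documents do not support it; the faults are the Abstract's label and a defence that leaves healing and regression to the mean unaddressed.

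Next, regression to the mean is a possibility, not a demonstrated fact. Entry includes people merely at risk, groups are sited using registers of leprosy and other chronic conditions, and nothing says people are chosen for a current ulcer. That also stands. A reader might infer that a spurious fall is certain or that its size is known. It is neither: with no excess at T0 the model gives zero.

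Third, the reason given in Study design fits control group 1, and control group 2 is introduced immediately afterwards, so the restriction may be loose drafting. Probably so, and it would go too far to say the data will never be collected. But the word *only* is explicit and conflicts with two other sections. A reader might also see a conflict over who belongs to control group 2, since Study design mentions only decliners affected by leprosy while Eligibility criteria admits any eligible decliner. Study design defers to the later description and excludes nobody, so this is drafting, not a second contradiction.

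Finally, it is tempting to make the change in members minus the change in decliners the main ulcer effect. The documents do not support that. Decliners are self-selected, perhaps through stigma, and may be absent in some clusters. If current ulcers prompt joining, decliners would not carry the same excess, so the contrast would keep the bias.

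**Conclusion.** The point holds in limited form. The Abstract claims a controlled evaluation of effectiveness on ulcers, whereas the hypothesis is an uncontrolled before-after comparison in about 180 members. The stated defence does not cover spontaneous healing or regression to the mean. The size of any resulting bias cannot be determined: it is zero if the ulcer share at T0 equals its long-run level, and 4 to 21 points if it is 10 to 30 points higher, under the assumed prevalence and correlation. Control group 2 cannot settle the question, with a half-width of about 15 points at its most optimistic size and 41 points with five people. It is still the only concurrent information, so the conflict over whether it is examined needs to be resolved before T0. This should be corrected; it does not touch the four generic outcomes, which have control group 1.

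**What to change.** 1. In Study design, state that clinical observations at T0, T1 and T2 cover people affected by leprosy in both the self-help group and control group 2, with membership of control group 2 as defined in Eligibility criteria.
2. In the Abstract and in Aim of the evaluation, describe the ulcer part as an uncontrolled before-after analysis that does not by itself establish effectiveness. Show control group 2 alongside as a descriptive, self-selected and imprecise comparator.
3. Report the share of members with an ulcer at T0, then ulcer change separately for those with one at T0 (healing) and those without (new ulcers). The split does not remove the bias, but it shows how much of a net fall is healing of ulcers present at entry.

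The cost is protocol wording and a less assertive ulcer conclusion. Item 3 uses data already planned, and item 1 adds no examinations beyond those that Quantitative data already foresees.
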